### Treatments

#### Treatment procedure

All participants receive regular SUD treatment plus either one of the following PTSD interventions: PE, EMDR or ImRs. SUD treatment starts directly after randomization for all participants. For patients allocated to the simultaneous treatment condition, PTSD treatment starts within 2 weeks after the start of the SUD treatment. For those in the sequential treatment condition, PTSD treatment starts 3 months after the start of the SUD treatment.

All PTSD treatments are provided by trained therapists and consist of twelve 90-min face-to-face sessions, conducted twice a week. Every treatment is executed by two different PTSD therapists, who alternately provide a session, inspired by the therapist rotation model. Among other things, this approach has shown to decrease avoidance behavior in sessions. Therefore, it is promising to improve trauma-focused treatment [37]. In all PTSD treatments, the focus of the first session is to present the treatment rationale and to list the traumatic experiences that will be addressed during the course of treatment. This overview is discussed and approved in peer-supervision after the first session. Henceforth the second session, each session contains 60 min of the specific intervention; EMDR, ImRs of PE. The rest of the session will be used to administer self-report questionnaires, to rehearse the rationale, to determine the specific trauma that will be addressed in the session and evaluation of the session. The self-report questionnaires are used to monitor symptom change during treatment. Although therapists encourage patients to be abstinent, this is not a requirement for the PTSD treatment. However, when a therapists notices a patients is intoxicated to such an extent that he/she has no capability to learn, the session is rescheduled.

#### PE

PE involves confrontation with distressing stimuli related to the trauma until anxiety is reduced. It is a manualized intervention including both imaginal and in vivo exposure components [38, 39]. Imaginal exposure uses confrontation to trauma memories through imagination, whereas in vivo exposure involves confronting real life situations that provoke anxiety and are avoided because of their association with the traumatic event. The aim of both is to extinguish the conditioned emotional response to stimuli associated with trauma [38]. Treatment sessions consist of 60 min of prolonged imaginal exposure (repeated recounting of the most anxiety provoking traumatic situations and related thoughts and feelings), and exposure in vivo (approaching trauma-related cues and situations). Between sessions, participants listen to audio recordings of the imaginal exposure on a daily basis, and complete in-vivo homework assignments. Within PE, only traumatic events that meet up the A-criterion of the DSM-5 can be included in the case conceptualization.

#### EMDR

EMDR is a manualized intervention, intended to reduce the liveliness of the traumatic memories and to change dysfunctional beliefs about self or others in terms of the traumatic event [40]. In the therapy the patient is asked to hold the distressing image in mind, along with the associated negative cognitions and bodily sensations, while engaging in saccadic eye movements. After approximately 20 s, the therapist asks the patient to note any changes occurring in the image, sensations, thoughts or emotions. This process is repeated until desensitization has occurred [40]. In this study the Dutch adaptation of Shapiro’s basic EMDR protocol is followed [41]. In this Dutch version, focus is more on reaching a high and optimal level of arousal instead of reassuring the patient, since high levels of emotional arousal have been found to enhance the memory-degrading effects of eye movements [42]. Therefore, the exercise of the safe place is absent in this version and rapidity of the procedures is higher. Furthermore, target selection is more extensively determined in the Dutch version [43]. Although traumatic events that meet the A-criterion of PTSD according DSM-5 will be addressed first, traumatic events that do not meet the A-criterion of the DSM-5 can also be addressed with EMDR, if there are still PTSD symptoms and sessions left.

#### ImRs

ImRs is a technique that changes the meaning of emotional memories and images (like intrusions and nightmares). With ImRs the individual is instructed to imagine the trauma memory as vividly as possible, as if it is happening in the here and now, and to imagine that the sequence of events is changed in a direction that the person desires [44]. The procedure aims to correct dysfunctional meanings attached to trauma memories and restore perceived control. The protocol is based on the ImRs protocol described by Arntz and Weertman [45]. In a minimum of two and a maximum of 5 sessions after the first session, the therapist steps into the image and rescripts, the patient staying in the perspective of their former self. After this, patients themselves rescript by stepping in the image from the perspective of their current self and intervening to protect and meet up with the needs of their former self. After completing this imagination of a new script, the patient experiences the new script from the perspective of their former self, during which they can ask for additional actions by their present self. The procedure of rescripting continues until the patient is satisfied. As with EMDR, traumatic events that do not meet the A-criterion of DSM-5 traumas can be addressed with ImRs, if there are still PTSD symptoms and sessions left.

#### Treatment completion and early responders

PTSD treatment completion is defined as a participant completing all 12 sessions of PTSD treatment within the allocated timeframe or being an early responder. For the simultaneous treatment condition, the timeframe for PTSD treatment is between baseline and 3-month follow-up. For the sequential treatment condition, the timeframe for the PTSD treatment is between 3-month and 6-month follow-up. Non-completers or drop-outs are participants who do not complete their PTSD treatment within the allocated timeframe. Participants who do not show for one of more treatment session are contacted by their therapists and motivated to commit to the treatment. Treatment is halted when a participant decides to stop or when the end of the timeframe is reached.

Early response is defined as agreement between the participant and therapists about being free of PTSD symptoms, a total score below 13 (items 1–20 minus items 15, 16, 19 and 20) on the PTSD checklist for DSM-5 (PCL-5) for 2 consecutive sessions and after consultation with at least one researcher and with colleagues in weekly peer-supervision. In case a participant in the sequential condition is free of PTSD symptoms at the first follow-up measure (T1), the participant will still start with the PTSD treatment until these criteria of early response are reached.

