#### Randomization and procedure

After the baseline assessment (T0), patients are randomly assigned to PE, EMDR, ImRs or SUD treatment only (each 25% chance). All patients receive SUD treatment shortly after the baseline assessment. Patients allocated to PE, EMDR or ImRs receive PTSD and SUD treatment simultaneously (75% of the sample), whereas patients in the 3-month SUD treatment only condition receive PTSD treatment after completing 3 months SUD treatment (25% of the sample). Patients in the SUD treatment only condition are randomly allocated to either PE (33% chance), EMDR (33% chance) or ImRs (33% chance) and start with the PTSD treatment after the 3 months follow-up assessment (T1).

After randomization, only disclosure of the timing will be given to the participants. Disclosure of treatment type will be done by the therapist at the start of the first session of the PTSD treatment.

Randomization is carried out by an independent researcher from Arkin who uses a computer-generated block randomization schedule. First patients are allocated to: simultaneous PE, simultaneous EMDR, simultaneous ImRs of sequential treatment with allocation probabilities per condition of 1/4. Block sizes are 4 and 8. Second, participants randomized to sequential treatment are allocated to: sequential PE, sequential EMDR or sequential ImRs, with allocation probabilities per condition of 1/3, after completion of the 3-months follow-up (T1) assessment. Block sizes are 3 and 6. Randomization is stratified by type of care (inpatient, daytreatment or outpatient) and location (Amsterdam or Utrecht). To prevent selection bias, all researchers are blind to order of block size and will not have access to the randomization schedule.

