#### Assessments

Assessments take place at baseline (T0), after 3 months (T1), 6 months (T2) and 9 months (T3). The T0 takes place within 1–2 weeks before the start of SUD treatment. Therefore, participants randomized to simultaneous SUD/PTSD treatment will receive PTSD treatment between baseline (T0) and 3-month follow-up (T1), whereas participants randomized to sequential SUD/PTSD treatment will receive PTSD treatment between 3-month (T1) and 6-month (T2) follow up. See also the flow chart in Fig. 1. All assessments are conducted by a junior researcher (MSc in Psychology), who is blind to treatment condition. In case of unblinding during an intermittent measurement, another assessor will administer the next measurement(s). All assessments consist of a 45–60 min interview-administered instrument to measure severity of PTSD symptoms (CAPS-5) and several self-report questionnaires. In total, assessments take 90–120 min to administer. All participants receive a gift voucher of €15 for each assessments to acknowledge the time and effort they provide in participating in the research. The self-report questionnaires that are administered are described in the following section and listed in Table 1.

**Table 1 Tab1:** Measurement instruments at every measurement moment

	Screening measurement	T0	T1	T2	T3

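### Within nominally equal 3-month windows, simultaneous patients can have less usable time for the 12 PTSD sessions, so equal attendance can give them a lower completion rate

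*Protocol article*

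**What the plan says.** The section on treatment completion and early responders sets the rule: "PTSD treatment completion is defined as a participant completing all 12 sessions of PTSD treatment within the allocated timeframe or being an early responder". It gives one window per condition: "For the simultaneous treatment condition, the timeframe for PTSD treatment is between baseline and 3-month follow-up", and "For the sequential treatment condition, the timeframe for the PTSD treatment is between 3-month and 6-month follow-up". It closes the window firmly: "Treatment is halted when a participant decides to stop or when the end of the timeframe is reached". Everyone unfinished falls into one class: "Non-completers or drop-outs are participants who do not complete their PTSD treatment within the allocated timeframe".

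The start of treatment is described elsewhere.

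- Assessments: "The T0 takes place within 1–2 weeks before the start of SUD treatment".
- Treatment procedure, simultaneous patients: "PTSD treatment starts within 2 weeks after the start of the SUD treatment".
- Randomization and procedure, sequential patients: they "start with the PTSD treatment after the 3 months follow-up assessment (T1"), and the draw between PE, EMDR and ImRs is made only once T1 is complete.
- Treatment procedure, sequential patients: the start is counted as three months from SUD start, not from T1.

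The course is 12 sessions at two per week. Completion is the first secondary outcome listed. Secondary outcomes are analysed along the same lines as the primary outcome, which includes the timing comparison (Objective 2). Completion rates will also be shown for all six randomized groups.

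**The concern.** The completion window is tied to assessments, not to the first PTSD session. For simultaneous patients it opens at T0, when neither SUD nor PTSD treatment has begun, so the waiting time is taken out of the window. For sequential patients it opens at T1, at or shortly before the point where PTSD treatment may begin. The same 12 sessions can therefore have different room for missed or rescheduled appointments in the two conditions.

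A patient still attending when the window closes is recorded in the same way as one who walked away. High drop-out is part of the trial's rationale, and the Background reports that some clinicians regard simultaneous treatment as counterproductive. A completion deficit produced by the measuring window could be read as evidence of poorer tolerability.

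**Working it through.** The plan states no window in weeks and no attendance rate, so there is no figure of its own to reproduce. Three months is taken as 13 weeks (91 days / 7), and assessments are assumed to fall on their nominal dates.

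**Step 1: usable weeks.** Usable weeks = 13 − delay from the opening assessment to the first PTSD session.

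- Simultaneous: 13 − (1 to 2 weeks to SUD start) − (0 to 2 weeks to PTSD start) = 9 to 12.
- Sequential, start after T1 (Randomization and procedure): at most 13 − 0 = 13. No lag after T1 is stated, so this is a ceiling.
- Sequential, start three months after SUD start (Treatment procedure): SUD starts 1–2 weeks after T0, so PTSD treatment starts 1–2 weeks after T1. Usable time is 13 − (1 to 2) = 11 to 12.

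On the last reading, compare patients with the same SUD delay. With a 1-week delay, simultaneous has 10–12 weeks and sequential 12; with a 2-week delay, 9–11 and 11. The shortfall is 0–2 weeks and can be nil.

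**Step 2: room in the schedule.** The course needs 12 / 2 = 6 weeks. Every window exceeds that. The pace required is 12/9 = 1.33 sessions per week for 9 weeks, 12/12 = 1.00 for 12 and 12/13 = 0.92 for 13.

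**Step 3: completion at equal attendance.** Assume two slots per week, each attended independently with probability p, missed slots re-offered until the window closes, nobody deciding to stop, and no early responders. Then P(complete) = P(X ≥ 12), with X ~ Binomial(2 × weeks, p). The values of p are assumptions.

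| p | 9 wk | 10 wk | 11 wk | 12 wk | 13 wk |
|---|---|---|---|---|---|
| 0.5 | 11.9% | 25.2% | 41.6% | 58.1% | 72.1% |
| 0.6 | 37.4% | 59.6% | 77.2% | 88.6% | 94.8% |
| 0.7 | 72.2% | 88.7% | 96.1% | 98.9% | 99.7% |
| 0.8 | 94.9% | 99.0% | 99.8% | 100% | 100% |
| 0.9 | 99.9% | 100% | 100% | 100% | 100% |

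**Step 4: average gap.** Weight 9, 10, 11 and 12 weeks equally for simultaneous. For sequential use 13 weeks, or the mean of 11 and 12. At p = 0.6, simultaneous is (37.4 + 59.6 + 77.2 + 88.6) / 4 = 65.7%.

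| p | Simultaneous | Sequential, 13 wk | Gap (points) | Sequential, 11–12 wk | Gap (points) |
|---|---|---|---|---|---|
| 0.5 | 34.2% | 72.1% | 38 | 49.8% | 16 |
| 0.6 | 65.7% | 94.8% | 29 | 82.9% | 17 |
| 0.7 | 89.0% | 99.7% | 11 | 97.5% | 9 |
| 0.8 | 98.4% | 100% | 1.6 | 99.9% | 1.5 |
| 0.9 | 100% | 100% | 0 | 100% | 0 |

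If both conditions had the same usable weeks, the gap would be zero by construction: at p = 0.6, 37% in both over 9 weeks or 89% in both over 12.

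**The case against.** The windows as written are equal: each is nominally 3 months, between consecutive assessments. Ending treatment before the next assessment has an obvious purpose, and whether the course was delivered within each strategy's planned period is a defensible thing to measure. The lags are loosely stated. Thirteen weeks would need a first session on the day of T1, yet sequential patients must first be randomized to a treatment type after T1. Six weeks of sessions in at least nine usable weeks leaves generous slack. The number of PTSD sessions attended is recorded, so patients cut off late could be described anyway.

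Most of this stands, and it rules out some stronger readings.

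- A reader might infer that the plan sets unequal windows of 9–12 against 13 weeks. It does not. Only usable time differs, and 13 is a ceiling.
- A reader might infer that equal attendance always lowers the simultaneous rate. At 90% attendance or more the model shows no material gap.
- A reader might take 94.8 − 37.4 = 57 points as the likely bias. That needs 60% attendance, the shortest simultaneous window and the longest sequential one together.

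The objection does not remove the direction. On the lags actually stated, simultaneous usable time is equal or shorter under either account of the sequential start. An unstated lag after T1 could narrow the difference, but the documents give none. Nor does ending treatment before T1 require completion to be compared only over unequal usable time. Missed slots are foreseen too: the article provides for rescheduling after intoxication and for contacting patients who do not show.

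**Conclusion.** The concern holds in limited form. The completion rule can favour the sequential condition at equal attendance, because simultaneous patients may have 9–12 usable weeks against at most 13, or 11–12. The size cannot be fixed from the documents. Under independent, re-offered slots and equal weighting over 9–12 weeks, the average gap is about 0–2 points at 80% attendance or more, 9–11 at 70% and 17–29 at 60%. It becomes material only if many slots are missed or rescheduled.

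The artefact is confined to patients cut off by the window. Those who decide to stop are non-completers whatever its length. A reader might extend the point to the primary analysis, but CAPS-5 severity is not defined through completion, so this misclassification does not enter it. Separately, the sections on treatment procedure, completion, randomization and assessments do not agree on when sequential PTSD treatment starts relative to its window.

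**What to change.** Keep the existing definition and make three changes.

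1. In the timing comparison of completion, report patients halted because the window closed separately from patients who decided to stop.
2. Add a completion analysis counted from the date of the first PTSD session, over the same number of weeks in both conditions. Fix that number before completion is examined by condition, and make it no longer than the shortest usable time. On the stated lags that is 9 weeks.
3. Reconcile the four sections on when sequential PTSD treatment and its window open. This review takes no position on which start rule is right.

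No extra visits are needed. Session counts are recorded and a checklist is registered at every session, so first-session dates should be recoverable. The reason for ending may need one more field. The downside is that a shorter common cut-off lowers the stated completion rate in both conditions, since some patients with all 12 sessions finish after it. That is why the new analysis belongs beside the present definition and not in its place. As the trial is already running, it should be labelled as an addition.

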#### Therapists and training

Therapists in this study are experienced and licensed master’s level psychologists. All therapists are trained in all three methods to avoid therapist effects. Before participation in the trial, therapists attended a two-day training in PE provided by [name], a 5 day training in EMDR provided by [name] and a two-day training in ImRs provided by [name]. After finishing the trainings, all therapists had to pass a treatment integrity assessment with pilot patients by handing in a video for each type of therapy to demonstrate their competence. During the study, all therapists receive weekly one-hour peer-supervision sessions and tree yearly two-hour supervision sessions: one with each of the abovementioned trainers. There are several highly experienced therapists in each peer-supervision group. When questions arise that cannot be solved in peer-supervision, the trainers are consulted.

#### Treatment fidelity

All treatments sessions are recorded on audio. A random selection of sessions will be rated for treatment fidelity by trained junior researchers, using fidelity rating scales that were constructed in consultation with the professionals who provided the therapist training, before the start of the trial. For each treatment type, we will determine adherence to the protocol and test whether the rated sessions contained more elements of the allocated treatment type compared to elements of the other treatment types, to test treatment differentiation. This will be done with a simple t-test or non-parametric test, depending on the distribution of the data.

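### The treatment-differentiation test is a simple test on rated sessions that makes no allowance for sessions sharing therapists and patients, and is not said to be paired

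*Protocol article*

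**What the plan says.** The Treatment fidelity section of the protocol article sets the unit: "A random selection of sessions will be rated for treatment fidelity by trained junior researchers". For each treatment type, adherence is determined and a differentiation test is planned, to "test whether the rated sessions contained more elements of the allocated treatment type compared to elements of the other treatment types". The method follows: "This will be done with a simple t-test or non-parametric test, depending on the distribution of the data".

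Two other sections describe how sessions are grouped. Under Treatment procedure, the PTSD treatments "consist of twelve 90-min face-to-face sessions, conducted twice a week", and "Every treatment is executed by two different PTSD therapists, who alternately provide a session". Under Therapists and training: "All therapists are trained in all three methods to avoid therapist effects".

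The article does not give the number of therapists, the number of sessions to be rated (in total, per patient or per therapist), or any variance or correlation for the fidelity scores.

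**The concern.** Two kinds of dependence are present, and the stated method mentions neither.

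- **Within a session.** On the natural reading, each rated session yields a score for allocated-type elements and a score for other-type elements. These are two measurements on one unit, so the contrast is a within-session difference.
- **Between sessions.** Up to twelve sessions can come from one patient, two therapists alternate within that patient, and a therapist can treat several patients and, being cross-trained, may deliver more than one type. Sessions in the same cluster are likely to resemble each other in how purely the treatment is delivered.

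The check matters because Objective 3 compares PE, EMDR and ImRs head to head, and cross-trained therapists could carry elements of one method into another. Some therapists may mix methods more than others. That is variation in the allocated-minus-other difference between therapists, which is the form of clustering that makes a session-level test overstate its precision.

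**Working it through.** The article states no sample size, alpha, power or standard deviation for the fidelity check, so there is no figure to reproduce. The calculation shows what the stated method would do under assumed inputs.

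**Inputs**

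- From the article: sessions are the rated unit, there are 12 sessions per course, and two therapists alternate per patient.
- Assumed: m = 5 rated sessions per therapist (10 as a variant); ICC of the within-session difference by therapist 0.05 to 0.20; within-session correlation of the two scores, rho, from -0.5 to 0.7; two-sided alpha 0.05.

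**Step 1: paired test that ignores clustering.** The outcome is the difference d = allocated minus other. With m sessions per cluster, the variance of the mean of d is multiplied by 1 + (m - 1) x ICC, so

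naive SE / true SE = 1 / sqrt(1 + (m - 1) x ICC).

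The approximate true error rate of a nominal 5% test is 2 x [1 - Phi(1.96 x ratio)].

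| m | ICC | 1 + (m - 1) x ICC | SE ratio | 1.96 x ratio | Approx. type I error |
|---|---|---|---|---|---|
| 5 | 0.05 | 1.20 | 0.91 | 1.79 | 0.07 |
| 5 | 0.10 | 1.40 | 0.85 | 1.66 | 0.10 |
| 5 | 0.20 | 1.80 | 0.75 | 1.46 | 0.14 |
| 10 | 0.05 | 1.45 | 0.83 | 1.63 | 0.10 |
| 10 | 0.10 | 1.90 | 0.73 | 1.42 | 0.16 |
| 10 | 0.20 | 2.80 | 0.60 | 1.17 | 0.24 |

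Simulation with 10 therapists and 5 sessions each agrees. The paired t-test rejects in 0.070 to 0.074 of null data sets at ICC 0.05 and 0.094 to 0.099 at ICC 0.10 (20,000 replicates per setting), and in 0.145 at ICC 0.20 (40,000 replicates). The signed-rank test behaves similarly: 0.141 at ICC 0.20 (5,000 replicates).

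The same formula applies to patients as clusters, with m the number of rated sessions per patient. If each cluster contributes one session, m = 1 and the ratio is 1.

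**Step 2: what does not cause a problem.** A therapist effect that raises or lowers both scores equally cancels in d. With such an effect present but an ICC of d equal to 0, the paired test keeps its level (simulated 0.048 to 0.052).

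**Step 3: if an independent two-sample test were used.** Without clustering, the ratio is 1 / sqrt(1 - rho):

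| rho | -0.5 | -0.3 | 0 | 0.3 | 0.5 | 0.7 |
|---|---|---|---|---|---|---|
| SE ratio | 0.82 | 0.88 | 1.00 | 1.20 | 1.41 | 1.83 |

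The standard error is too small if rho is negative and too large if it is positive. Simulated type I error is 0.087 at rho = -0.3 and 0.007 at rho = 0.5. With rho = 0.5 and an ICC of 0.10 it is 0.014 to 0.027, so the test stays conservative despite the clustering.

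**Step 4: respecting both.** Testing the therapist means of d returns the error rate to 0.047 to 0.054 in the scenarios with ICC 0 to 0.10, and to 0.049 at ICC 0.20.

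**The case against.** The strongest reply is that the article never says the test is independent. A paired t-test is a simple t-test and the signed-rank test is non-parametric, so the wording admits the version that suits the within-session contrast. This stands. A reader might infer that ignoring the pairing makes the error bars too narrow, perhaps because the 60 minutes of intervention are shared between allocated and other elements. The document does not support that: it does not commit to an unpaired test, and step 3 shows the direction depends on the sign of a correlation it does not give.

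Second, the effect of clustering is conditional and its size cannot be computed from the article. This also stands, and the ranges above are labelled as assumptions for that reason.

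Third, the null hypothesis has little practical interest. Therapists had to pass an integrity assessment by video for each therapy, each session from the second on reserves 60 minutes for the specific intervention, and adherence is rated separately. A very large difference is the expected result and would remain significant. This limits the importance of the point, but the precision of the estimated difference would still be overstated for any type where separation is modest.

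Fourth, details of a fidelity check may belong in a fuller document. Here, however, the article does name the method and makes distributional shape the only criterion of choice. Switching from a t-test to a rank test does not address dependence between sessions.

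**Conclusion.** The point holds as a minor one. The stated differentiation test is not specified as paired and takes no account of sessions sharing therapists and patients. Under even the favourable reading, a paired test, its standard error is too small if the allocated-minus-other difference varies by therapist or patient and more than one session per cluster is rated. With 5 sessions per therapist and an ICC of 0.05 to 0.20, the understatement is 9% to 25% of the true standard error (ratios 0.91 to 0.75), with a type I error of about 7% to 14% at a nominal 5%. More rated sessions per therapist would make this worse; one per cluster would remove it.

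A reader might go further and infer that the head-to-head results are affected. They are not: Objective 3 does not use this test, and no effectiveness estimate, sample size or alpha depends on it.

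**What to change.** Define the outcome as the within-session difference, allocated minus other elements. For each treatment type, fit a mixed model with random effects for therapist and patient, use small-sample degrees of freedom because therapists may be few, and report the mean difference with its 95% interval. A mean alone averages over therapists, so if mixing by individual therapists is of interest, also report the between-therapist variance or the therapist-level means.

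The cost is a few lines of analysis code and slightly wider intervals. No further sessions need rating, provided therapist and patient identifiers are kept with each rated session.
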